##### Communication skills from simulation patients’ perspective

Participants’ communication skills during an SPA will be assessed by the simulated patient using several items of the short version of the German measure *Experienced Patient-Centeredness Questionnaire* (EPAT) [44]. This measure assesses experienced patient-centeredness and has recently been developed and psychometrically tested by the research team. Items can be answered on a 6-point-Likert scale from 1 (“completely disagree”) to 6 (“completely agree”). It will be assessed four weeks after the training directly after performing the SPA (t2).

##### Self-assessed communication skills

Participating nurses will assess their own communication skills during SPAs by rating several items of the EPAT [44], which will be adapted to HCPs by the study team. This measure will also be assessed four weeks after the training directly after performing the SPA (t2).

##### Professional fulfillment

Nurses’ professional fulfillment and overall burnout will be assessed using the 16-item *Professional Fulfillment Index* (PFI) [45]. This three-dimensional measure comprises three main scales (‘HCP’s professional fulfillment’, ‘work exhaustion’ and ‘interpersonal disengagement’) as well as an overall burnout score. Items can be answered on a scale from 0 (“not at all”) to 4 (“extremely”). A German version of the PFI was recently translated and adapted by the research team. The PFI will be assessed at all measurement points (t0, t1, t2).

##### Depression and anxiety

To assess symptoms of depression and anxiety, the German version of the *Patient Health Questionnaire 4* (PHQ-4) [46] will be applied. The PHQ-4 is a two-dimensional scale with four items, which can be rated on a scale from 0 (“not at all”) to 3 (“nearly every day”). The PHQ-4 will be assessed at all measurement points (t0, t1, t2).

##### Subjective working capacities

Participants’ subjective working capacities will be assessed via two dimensions of the German version of the *Work Ability Index* (WAI) [47]. Dimension one (‘subjective estimation of current work ability compared with lifetime best’) comprises one item and can be answered on a scale from 1 (“totally unable to work”) to 10 (“best working capacity”). Dimension two (‘subjective work ability in relation to job demands’) comprises two items and can be answered on a scale from 1 (“very bad”) to 5 (“very good”). The WAI will be assessed at all measurement points (t0, t1, t2).

##### Impact of contamination

To measure the impact of contamination, a self-developed item will assess the extent to which participants from CG have received information about the trainings’ content from colleagues of the IG. This item will be assessed in the CG at all measurement points (t0, t1, t2) and in the IG only at baseline (t0).

##### Perceived patient-centeredness of healthcare settings

Perceived patient-centered quality of the care environment within the wards, participants are working in, will be assessed using the short version of EPAT [44], which was adapted for HCP. This measure will be assessed prior to the training (t0) and four weeks after the training (t2).

#### Process evaluation

The purpose of the process evaluation is to analyze deviations from the study protocol as well as factors which influence the roll-out of the CST (e.g. barriers and facilitators). Based on results of the process evaluation, indications for a future implementation of the CST should be derived. We will use the CFIR [19] as well as implementation outcomes defined by Proctor et al. [48] to guide the process evaluation.

For process evaluation, qualitative and quantitative data will be collected during the entire course of the RCT. Qualitative data will include [1] field notes of the research team regarding observations of interactions between members of the research team and clinical stakeholders, participant recruitment and data collection processes, [2] minutes of research team meetings regarding data collection during process evaluation, and [3] short interviews with clinical stakeholders who participated and who did not participate in the CST, applying a purposive sampling strategy with maximum variation approach. For those, clinical stakeholders of different professions and different hierarchy levels will be included and interviews will be audio-recorded. Those data will gain insights in e.g. acceptability, appropriateness and feasibility of the CST. Quantitative data will include quantitative key indicators on dropout rates, training participation, duration, and numbers of trainings per department. Those data will gain insights into reach, dose and fidelity of the CST and could be used to adapt the process of CST roll-out to promote participant retention throughout the whole study if necessary.

### Data monitoring

The process of data collection and management will be documented by the research team continuously during all measurement points. In regular meetings, the process will be discussed and adjustments will be made if necessary. All data will be stored at a secure server of the department of Medical Psychology. Only members of the research team have access to the secure server. To ensure data protection throughout the trial, a data protection protocol was conducted. Data deletion is carried out using a data-cleaning protocol.

### Data analysis

Prior to analysis of quantitative data, a missing data analysis will be conducted and cut-off criteria for including instruments in analysis will be applied. Multiple imputation will be used to handle remaining missing data. Descriptive outcome analysis and process evaluation will be performed by calculating frequencies and percentages for categorical data, medians and interquartile ranges for ordinal or non-normally distributed quantitative data, and means and standard deviations for approximately normally distributed data. Quantitative outcomes will be analyzed by linear mixed models including treatment group, time, and their interaction as fixed effects. Hierarchical data structures (e.g., clustering within departments) will be accounted for by letting the intercept vary randomly across clusters. Categorical and ordinal outcomes will be analyzed by corresponding models which use an appropriate link (e.g., logistic for binary variables). We will report 95 percent confidence intervals for all estimated parameters. The level of statistical significance for the primary confirmatory analysis will be set at p<.05. All other analyses will be considered exploratory. Qualitative data of the process evaluation will be analyzed according to principles of content analysis [49]. Quantitative data of outcome and process evaluation will be entered into and analyzed with SPSS (IBM SPSS Statistics, V.23) by members of the research team consecutively. To ensure high data quality, 20% of the quantitative data will be entered double for quality control. Qualitative data of process evaluation will be imported into and analyzed with MAXQDA software (VERBI GmbH, Berlin, Germany).

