#### Sample size

Based on results of previous studies on effects of CSTs on self-efficacy of nurses, we aim to identify a moderate effect of the intervention (Cohen’s d of 0.50) on the primary outcome [28, 29]. To identify this effect in a two-sided test with an alpha error probability of 0.05 and a power of 0.80, data from a total sample of 128 participants (64 participants per group) are needed. In order to be able to account for missing data due to participant dropout, for potential differences between treatment groups at baseline, and for clustered data structures, we aim to recruit a total of 180 participants (90 participants in each group).

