#### Recruitment and randomization

Nurses will be recruited continuously starting in November 2022 until spring 2024 within their departments. Therefore, we contact heads of relevant departments at the UKE by e-mail and ask them to forward the study information to all eligible staff in the respective department. Prior to study participation, eligible nurses will be informed that there is an equal chance to be assigned to the IG or CG. After giving informed written consent, they will be asked to complete the baseline assessment (t0). Afterwards, participants will be randomized in a 1:1 ratio to either IG or CG. For this purpose, stratified randomization will be applied [30]. Each department of the UKE will be defined as a stratum. A member of the research team, who will not be involved in recruitment of eligible nurses, will allocate participating nurses within each stratum to either IG or CG by using permuted blocks. Participating nurses of the CG are offered to participate in the training after data collection has been completed.

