#### Primary outcome

As the primary outcome, we chose self-efficacy regarding nurses’ communicating with patients. According to Albert Bandura (1997) self-efficacy is the belief in one's own ability to successfully deal with certain tasks or situations [32]. *S*elf-efficacy has been shown to be positively related to HCPs’ performance in communication [33]. Thus, the concept of self-efficacy has been frequently used to assess the impact of CST on HPs [11, 33, 34]. Self-efficacy regarding communication skills with patients will be assessed using the German version of the 12-item *Self-Efficacy of Communication Skills scale (SE-12).* The original scale was developed by Axboe et al. [35] and has already been used as primary outcome in other studies to evaluate CSTs for nurses [11]. Items on this one-dimensional scale can be answered on a scale from 1 (“very uncertain”) to 10 (“very certain”) with an additional option to rate items as “not relevant”. In a previous study by the research team, the SE-12 was translated and adapted into German following the team approach consisting of translation, review, adjudication, pretesting and documentation (TRAPD) [36] and psychometrically tested by Frerichs et al. [37]. Self-efficacy will be assessed at all measurement points (t0, t1, t2), with t1 being the primary endpoint.

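### The stated group-by-time model gives the pre-randomisation SE-12 a free group difference; a single t1 contrast adjusted for t0 would be more precise at no cost

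*Protocol article*

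**What the plan says.** Four places in the protocol article bear on this point.

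- **Data analysis** gives the fixed effects: "Quantitative outcomes will be analyzed by linear mixed models including treatment group, time, and their interaction as fixed effects". It adds a random intercept across clusters, with departments as the example, and a 0.05 level for the primary confirmatory analysis. It names no t0 covariate, no common t0 mean, and no coefficient or contrast for the primary test.
- **Primary outcome** has SE-12 assessed at t0, t1 and t2, "with t1 being the primary endpoint".
- **Recruitment and randomization** fixes the order of events: after consent, "they will be asked to complete the baseline assessment (t0). Afterwards, participants will be randomized in a 1:1 ratio to either IG or CG".
- **Sample size** aims at a Cohen's d of 0.50 "in a two-sided test with an alpha error probability of 0.05 and a power of 0.80", for which "data from a total sample of 128 participants (64 participants per group) are needed". The recruitment target is 180 (90 per group). The increase is meant to cover dropout, clustering and allowance "for potential differences between treatment groups at baseline", with no figure for any of the three.

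**The concern.** Because t0 is completed before allocation, any difference between the arms at t0 is chance, and the true difference is zero by design. A model with group, time and their interaction over all three occasions nevertheless estimates that difference freely. It gives up the information that a correlated pre-randomisation measure carries about t1.

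Two single-degree-of-freedom effects at t1 can be read from such a model: the t1-versus-t0 interaction coefficient, and the group difference at t1. Both are less precise than a baseline-adjusted t1 contrast. What is at stake is the precision of the only confirmatory test and, in one part of the range, the planned 80% power. Since no contrast is named, a joint test of both interaction terms also remains open, and that test would not address the t1 endpoint alone.

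**Working it through.** **Inputs from the article:** d = 0.50, two-sided alpha 0.05, power 0.80, 64 analysed and 90 recruited per arm (Sample size); three occasions with t1 primary (Primary outcome); t0 before randomisation (Recruitment and randomization).

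**Assumptions:** the t0-t1 correlation rho of SE-12 is not in the article, so 0.3, 0.5 and 0.7 are used. SD is 1 at each occasion, correlation is equal between occasions, data are complete, clustering is ignored, and within-person correlation is modelled.

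**1. The plan's own figure.** A two-sample t-test with d = 0.50 needs 63.77 per arm, so 64, with power 0.801. The stated 128 reproduces as a plain two-group comparison. The normal approximation used below gives 63 per arm, and 0.807 at 64.

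**2. Variance factors V**, where the variance of the estimate is V x 2/n:
- t1-versus-t0 interaction coefficient: V = 2(1-rho), the change score.
- Group difference at t1 from the same model: V = 1.
- t0 as covariate, or t0 means constrained equal: V = 1-rho^2.

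A generalised least squares calculation on the three-occasion model returned exactly these values.

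**3. Efficiency loss against baseline adjustment**, 1 - V(adjusted)/V(reading):
- Interaction: 1 - (1-rho^2)/(2(1-rho)) = 1 - (1+rho)/2 = (1-rho)/2.
- t1 difference: 1 - (1-rho^2) = rho^2.

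| rho | V interaction | V t1 difference | V adjusted | Loss, interaction | Loss, t1 difference |
|---|---|---|---|---|---|
| 0.3 | 1.40 | 1.00 | 0.91 | 35% | 9% |
| 0.5 | 1.00 | 1.00 | 0.75 | 25% | 25% |
| 0.7 | 0.60 | 1.00 | 0.51 | 15% | 49% |

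Outside this range the interaction loss is 40% at rho 0.2, 10% at 0.8 and 5% at 0.9.

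**4. Sample size and power.** n per arm = 2(1.96 + 0.842)^2 V / 0.50^2, which is about 62.8 V. Power = Phi(0.50 x sqrt(n/2)/sqrt(V) - 1.96). Example for the interaction at rho 0.3 and n = 64: 0.50 x 5.657/1.183 - 1.96 = 0.43, so power is 0.667. Each cell below gives interaction / t1 difference / adjusted.

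| rho | n per arm for 80% | Power at 64 per arm | Power at 90 per arm |
|---|---|---|---|
| 0.3 | 88 / 63 / 58 | 0.667 / 0.807 / 0.843 | 0.809 / 0.918 / 0.940 |
| 0.5 | 63 / 63 / 48 | 0.807 / 0.807 / 0.904 | 0.918 / 0.918 / 0.972 |
| 0.7 | 38 / 63 / 33 | 0.955 / 0.807 / 0.977 | 0.991 / 0.918 / 0.997 |

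At rho 0.4 the interaction contrast has power 0.733 at 64 per arm and needs 76 per arm for 80%. Only at rho 0.2, below the range shown, is power under 80% even with all 90 per arm analysed (0.755; 101 needed).

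**5. If both interaction terms were tested jointly.** With no effect at t1, d = 0.5 at t2, rho = 0.5 and 64 per arm, the covariance matrix of the two contrasts is [[1, 0.5], [0.5, 1]]/32. The non-centrality is 32 x (4/3) x 0.25 = 10.67, and the 2-df test rejects with probability 0.841. Such a test could succeed on t2 alone.

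**The case against.** The strongest reply is that the article commits to less than a critic might attribute to it.

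- **Change score.** A reader might infer that the primary analysis is a change-score analysis. The Data analysis section does not say that the interaction coefficient is the primary estimate. On the other reading, the group difference at t1, V is 1 and the 64-per-arm calculation matches the analysis at every rho. This stands. It does not rescue precision, because that reading loses rho^2.
- **Omnibus test.** A reader might infer a 2-df interaction test. None is mentioned. Confidence intervals are promised for all estimated parameters, and the Primary outcome section fixes t1, so a single t1 contrast is the natural joint reading. The exact contrast may also stand in a fuller document not shown here. This stands: the joint test is something to rule out, not something the plan states.
- **Underpowered trial.** A reader might infer that 80% power is not met. At 90 per arm the interaction contrast still has 0.809 at rho 0.3, and at rho 0.5 or above 64 per arm suffices. This largely stands. The extra participants are also meant to absorb dropout and clustering, however, and neither is quantified.
- **Validity.** A group-by-time mixed model is a valid analysis. With t0 before randomisation, its t1 effect is unbiased, and this choice does not inflate type I error. This stands in full.
- **Baseline differences in the sample-size text.** One might ask for that reason to be struck out. It is one of three reasons for an unitemised allowance, and deleting it would change no number, so it is an editorial matter.

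**Conclusion.** The point holds as one of precision. The model, as the article states it, leaves the t0 group difference free and names no baseline adjustment. For any rho strictly between 0 and 1, both single-contrast readings at t1 are less precise than adjusting for t0 SE-12, so the recommendation does not depend on which was intended.

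The losses are (1-rho)/2 and rho^2 respectively. The percentages rest on an assumed rho and should not be quoted as facts about this trial. For rho from 0.3 to 0.7, power below the stated 80% arises only with the interaction contrast, only for rho below about 0.5, and only if the analysed sample falls from 90 towards 64 per arm. The tolerated fall is small at rho 0.3 (88 needed) and larger at 0.4 (76 needed). The documents do not support a claim of bias, of a planned omnibus test, or of an underpowered trial.

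**What to change.** In Data analysis, state that the primary analysis is the between-arm difference in SE-12 at t1, tested as one contrast at two-sided 0.05. It should come from either:

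- a model with t0 SE-12 as covariate and t1 and t2 as outcomes, or
- a constrained longitudinal model with a common t0 mean in both arms and arm effects at t1 and t2 only.

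Keep the random intercepts for clustering as planned. Use the same form, with the appropriate link, for the other outcomes that have a t0 value: knowledge, attitudes, professional fulfilment, depression and anxiety, and working capacities. For attitudes, which are measured at t0 and t2 only, the contrast is at t2. Outcomes from the standardised patient assessment have no t0 value and are unaffected.

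Naming this contrast aligns the test with the t1 endpoint and rules out a joint 2-df interaction test. The cost is analysis wording, to be settled before the outcome data are analysed. SE-12 at t0 is already collected, and no participants, visits or measures are added.

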**Fig. 2 Fig2:**
[figure not shown]
Content, didactic methods and general conditions of the training to enhance nurses’ patient-centered communication skills

The training will be piloted with 8 to 12 nurses and other experts in the field of training development and finalized afterwards. It will be carried out in groups of 10 to 14 participants each and conducted by two trainers. The number of participants per training group will be planed slightly higher with 14 participants, as experience has shown that some participants cancel at short notice. One of the trainers will be a member of the research team with comprehensive experience in CSTs, as well as experience in communicating with patients. The second trainer will be a nursing professional, recently working at the UKE. We will use a train-the-trainer approach, meaning nurses will be trained in order to be able to conduct the communication skills training together with the research team. The train-the-trainer approach was found to enhance implementation success and sustainability of CST interventions [13].

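### Training groups exist only in the intervention arm and only after baseline, and the planned cluster intercept does not properly account for them; if outcomes correlate within groups, the primary standard error will be too small

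*Protocol article*

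**What the plan says.** All references are to the protocol article.

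- **Delivery (Intervention).** On the training: "It will be carried out in groups of 10 to 14 participants each and conducted by two trainers". Participants do role plays and group discussions and receive feedback from each other and from the trainers.
- **Allocation (Recruitment and randomization).** Nurses are randomised individually, 1:1. "Each department of the UKE will be defined as a stratum". The control group (CG) is offered the training only once data collection is complete, so it has no training groups at t1 or t2.
- **Endpoint (Primary outcome; Outcomes and measures).** SE-12 is measured at t0, t1 and t2. The primary endpoint is t1, directly after the training.
- **Model (Data analysis).** Linear mixed models with group, time and their interaction as fixed effects. On clustering: "Hierarchical data structures (e.g., clustering within departments) will be accounted for by letting the intercept vary randomly across clusters". The training group is not named as a cluster here or elsewhere.
- **Sample size.** "data from a total sample of 128 participants (64 participants per group) are needed". Recruitment is raised to 180 for dropout, for baseline differences and "for clustered data structures, we aim to recruit a total of 180 participants (90 participants in each group"). The section gives no ICC, design effect or dropout rate, and does not split the increase between the three reasons.

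**The concern.** This is a partially nested design. IG nurses share a session, two trainers and each other's feedback, while CG nurses are independent of one another apart from department. Session-mates may therefore have correlated SE-12 scores at t1. That correlation adds variance to the IG mean, and the analysis has to carry it.

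The department is not the level that causes this problem. Both arms occur within each department, so the department effect is common to both sides of the comparison, and adjusting for it helps precision if anything. It leaves a session effect in one arm untouched.

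At stake is the trial's one confirmatory test. A standard error that is too small gives confidence intervals that are too narrow and a false-positive rate above the stated 5%.

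**Working it through.** **1. The plan's own figure.** Inputs from Sample size: "we aim to identify a moderate effect of the intervention (Cohen’s d of 0.50) on the primary outcome", with a two-sided test, "an alpha error probability of 0.05 and a power of 0.80". The two-sample noncentral t calculation gives power 0.795 at 63 per arm and 0.801 at 64. The stated 64 per group (128 in total) is reproduced. It assumes no clustering.

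**2. Number of sessions.** For 90 IG nurses, 90/14 = 6.4 and 90/10 = 9, so about 6 to 9 sessions.

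**3. Effect of leaving sessions out.** Let m be the session size and ICC the share of t1 variance due to session (assumed).
- IG design effect: DE = 1 + (m − 1) × ICC. The CG design effect is 1.
- With equal arms, true SE / model SE = R = √((DE + 1)/2).
- Shortfall of the model SE = 1 − 1/R.
- Actual type I error = 2 × (1 − Φ(1.96/R)).

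For m = 12:

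| ICC | DE | R | True SE above model SE | Model SE too small by | Type I error |
|---|---|---|---|---|---|
| 0 | 1.00 | 1.000 | 0% | 0% | 5.0% |
| 0.01 | 1.11 | 1.027 | 3% | 3% | 5.6% |
| 0.02 | 1.22 | 1.054 | 5% | 5% | 6.3% |
| 0.05 | 1.55 | 1.129 | 13% | 11% | 8.3% |
| 0.10 | 2.10 | 1.245 | 25% | 20% | 11.5% |

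Over m = 10 to 14, type I error runs from 7.7% to 8.9% at ICC 0.05 and from 10.4% to 12.7% at ICC 0.10.

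**4. Does a department term help?** This was simulated with 10 departments of 18 nurses, baseline adjustment, department in the model, an IG-only session effect at t1, and 8,000 runs per setting. For ICC 0 / 0.01 / 0.02 / 0.05 / 0.10, type I error was:
- sessions of 12 mixing departments: 4.6% / 5.8% / 6.4% / 8.9% / 14.2%;
- sessions of 9 formed within departments: 5.0% / 5.9% / 6.8% / 8.5% / 12.4%.

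The department term does not remove the error. Some values exceed those in step 3 because baseline and department adjustment remove other variance, so the session component becomes a larger share of what remains.

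**5. Does a time-constant session intercept help?** In the t1-minus-t0 group-by-time contrast, anything constant over time cancels, so such an intercept adds nothing to that contrast's standard error. The session effect is absent at t0 and present at t1, so it stays in the contrast. With unit variance at each visit and t0–t1 correlation ρ (assumed), the change has variance 2(1 − ρ), and its ICC is the session variance divided by 2(1 − ρ). For m = 12 and session variance 0.02 / 0.05 / 0.10:
- ρ = 0.5: ICC of the change is 0.02 / 0.05 / 0.10, and type I error is 6.3% / 8.3% / 11.5%;
- ρ = 0.7: ICC of the change is 0.033 / 0.083 / 0.167, and type I error is 7.2% / 10.5% / 15.7%.

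A simulation with 84 per arm and 7 sessions of 12 agrees: 6.2% / 8.7% / 11.3% and 6.9% / 10.5% / 15.6%.

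**6. What the increase to 180 can cover.** With an assumed 20% dropout, 180 × 0.8 = 144, and 144/128 = 1.125. Setting (DE + 1)/2 = 1.125 gives DE = 1.25 and ICC = 0.25/(m − 1), which is 0.028, 0.023 and 0.019 for m = 10, 12 and 14. This is before any gain from baseline adjustment.

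**The case against.** The strongest reply is that the article does not commit to a department-only model. Departments are introduced as an example, and a fuller analysis plan may list the training group among the random effects. That stands: a session term is neither stated nor excluded, and an incomplete list in a condensed article would not be a finding by itself. What remains is the device the article does fix, a random intercept across clusters, which does not properly fit an effect confined to one arm and to the period after t0.

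A second reply is that the article does not say the t1-minus-t0 interaction contrast is the primary test. If the model-based group difference at t1 is tested instead, a session intercept does not cancel. That is correct, but an intercept held constant from t0 to t2 still describes the post-baseline correlation imperfectly.

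Three stronger readings are tempting, and the article does not support them.
- That the primary standard error is too small as a matter of fact. This requires a session ICC above 0, and none is given.
- That the increase from 128 to 180 is wasted on a clustering term missing from the analysis. The increase has three stated reasons and no split, and a larger N protects power whatever the model.
- That the trial is therefore underpowered. Power figures that ignore baseline do not describe the planned model, which uses t0.

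**Conclusion.** The point holds in conditional form. The one named cluster is the wrong level for this problem, and a time-constant intercept is a poor device for an effect that exists in one arm and only after baseline. If outcomes correlate within sessions, the confirmatory test is anti-conservative: slightly at ICC 0.01 (5.6%), materially at 0.05 to 0.10 (8.3% to 11.5% with 12 per session), and not at all at ICC 0. The ICC values, the t0–t1 correlations and the 20% dropout are assumptions; session size, arm structure, endpoint timing and model form come from the article. The larger N does not correct the standard error or the type I error. The change is recommended rather than essential, with moderate confidence, because the size depends on an unknown ICC and the article leaves room for a session term.

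**What to change.** - **Primary model.** Add a random effect for training session in the IG only, acting at t1 and t2 and not at t0, with each CG nurse treated as a singleton. Use Satterthwaite or Kenward-Roger degrees of freedom, because there will be only about 6 to 9 sessions. Keep department as the stratification term.
- **Data.** Record which session each IG nurse attended. The Process evaluation section lists training participation and numbers of trainings per department, but does not expressly provide for a session identifier per nurse.
- **Sample size section.** State the dropout and session ICC that 180 is meant to cover. For example, 20% dropout leaves room for an ICC of about 0.02 to 0.03 before any gain from baseline adjustment. Do not change N.

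The cost is one extra variable, a change to the analysis wording, and somewhat wider confidence intervals.
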